## Abstract

**Background:**

Although supervised exercise is frequently recommended for older adults, its superiority over unsupervised exercise remains uncertain. Furthermore, whether motivational techniques could help to enhance the effectiveness of the latter remains to be elucidated. The present randomized controlled trial aims to determine the role of supervision and motivational strategies on the safety, adherence, efficacy, and cost-effectiveness of different exercise programs for improving physical and mental health in older adults.

**Methods:**

Participants (*n* = 120, aged 60–75 years) will be randomly allocated into five groups: 1-Control (CON), 2-Supervised exercise without motivational intervention (SUP), 3- Supervised exercise with motivational intervention (SUP +), 4- Unsupervised exercise without motivational intervention (UNSUP) and 5- Unsupervised exercise with motivational intervention (UNSUP +). Over 24 weeks, all exercise groups will participate in a multicomponent exercise program three times/week (performed in group classes at a center for SUP and SUP + , or home without supervision but with the help of a mobile app for UNSUP and UNSUP +), while the CON group will maintain their usual lifestyle. The motivational intervention (for SUP + and UNSUP + groups) will be based on the self-determination theory, including strategies such as phone calls, interactive workshops, motivational messages, informative infographics and videos. Primary outcomes will include safety, adherence, costs, and lower-body muscular function using a leg press machine. Secondary outcomes will include upper-body muscular function, physical and cardiorespiratory function, blood pressure and heart rate, body composition, health-related quality of life, cognitive performance, anxiety, depression, physical activity levels, sleep and sedentarism, biochemical markers, motivators and barriers to exercise. Assessments will be conducted at baseline, mid-intervention (*i.e.,* week 13), at the end of the intervention (*i.e.,* week 25), and 24 weeks later (*i.e.,* week 49).

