### Sample size

The sample size was determined by a priori power analysis using G ∗ Power 3.1.9.4 software. Input parameters were entered considering repeated measures ANOVA (group by time interaction), setting the probability of α error at 0.05, 1-β = 0.80, and 5 groups. The standardized mean difference used for calculations was 0.43, based on the effect of home-based exercise on lower-body muscle power in older adults reported in a previous meta-analysis [19]. The model indicated a total sample size of 100 individuals, and considering a dropout rate of 20%, we finally decided to enroll 120 participants.

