##### Lower-body muscular function

The force–velocity relationship and the rate of force development (RFD) will be assessed unilaterally on a horizontal leg press machine (Selection MED, Technogym, Italy) instrumented with a force plate (Type 9286BA, Kistler, Switzerland) and a linear position transducer (TForce System, Ergotech, Spain). A familiarization session will be performed on the first day of assessments. During the RFD test, participants will receive instructions to execute multiple maximal voluntary isometric contractions. They will be required to rapidly and forcefully extend their knee while maintaining the contraction for 3 s following the cue *"Ready, set, go!"* [48].

Four adequate trials (avoiding countermovement before contraction onset), separated by 60 s will be acquired alternatively (knee angles of 90º and 120º). The maximal isometric force and RFD will be calculated as the linear slope of the time-force curve over different time intervals (0–400 ms) and at the maximal point of the time-RFD curve (RFDmax) [49]. To assess the force–velocity relationship, participants will perform a progressive loading test (5–20 kg increments) with 2 repetitions per load (leaving a few seconds between repetitions to ensure peak performance on the subsequent repetition), starting at approximately 40% of the individual one repetition maximum (1-RM) (corresponding to the first load in which there is no flight phase) until reaching a load equivalent to 80% 1-RM. Loads will be interspersed by 1-min of passive recovery. From the starting position (90º knee angle), participants will be instructed to perform the concentric phase of each repetition as fast and as strong as possible, regardless of the load used. The values of force and velocity of the most powerful repetitions with each load will be fitted by a linear model through the Excel spreadsheet of Alcazar et al. [50] from which we will estimate the theoretical maximal isometric force and the maximal velocity without load (intercepts of force and velocity, respectively). In addition, we will estimate the maximum muscular power as well as the force and velocity at which it is produced [51].

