### Statistical analysis

Data will be preferentially presented as mean ± standard deviation or as proportions for continuous and categorical variables, respectively. Data normality will be assessed by the Kolmogorov–Smirnov test and will be log-transformed in case of non-normal distribution. Baseline differences will be assessed through a one-way ANOVA. A two-way mixed ANCOVA (group [*i.e.*, CON, SUP, SUP + , UNSUP, and UNSUP +] x time [*i.e.,* baseline, mid, post-intervention, and follow-up assessments]) will be performed, adjusting for baseline values as well as for any other sociodemographic/descriptive variables that may differ between groups (*e.g.,* age, sex). Subsequent post-hoc tests will be conducted to determine which groups significantly differ. Effect sizes will be calculated to assess the magnitude of the differences [87]. Falls and fall-related injuries will be presented as rates/person (ITT analysis) and rates/person/year (± 30 days; PP analysis), and as numbers. Adverse events and dropouts will be compared between groups through Chi-squared tests. Differences in adherence rates will be analyzed using an ANOVA test. Correlation analyses will be used to assess associations between motivators, barriers, and adherence to exercise sessions. Whenever possible, statistical analyses will be performed on an intention-to-treat (ITT) basis (including all randomized participants). The potential effects of missing values and dropouts will also be explored using multiple imputation and sensitivity analyses [88]. As recommended, a complementary per protocol (PP) analysis will be performed (*i.e.,* including only those participants with valid data for baseline and post-intervention assessments and an adherence to exercise program of at least 80%) [89]. SPSS version 24.0 (IBM Corp., Armonk, NY) will be used for statistical analysis, and the significance level will be set at p ≤ 0.05 for all tests.

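### The primary outcome lower-body muscular function is an unranked family of about nine leg-press variables, each tested at 0.05, although the trial was sized on one of them

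*Protocol article*

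**What the plan says.** The abstract and the Outcome measures section name four primary domains without ranking them: "Primary outcomes will include safety, adherence, costs, and lower-body muscular function using a leg press machine".

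The subsection Lower-body muscular function fills the last domain with two tests.

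- **Isometric test, at knee angles of 90º and 120º.** Maximal isometric force and rate of force development (RFD) are obtained, the latter "calculated as the linear slope of the time-force curve over different time intervals" and also at its peak (RFDmax).
- **Force–velocity test.** A straight line is fitted, and its force and velocity intercepts are reported. In addition, "we will estimate the maximum muscular power as well as the force and velocity at which it is produced".

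No variable and no visit is singled out. Under Statistical analysis, "the significance level will be set at p ≤ 0.05 for all tests". That section describes a group-by-time ANCOVA followed by post-hoc tests whose method is not named.

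The Sample size section works from one quantity only, the effect of home-based exercise on lower-body muscle power: "The standardized mean difference used for calculations was 0.43". The error rates were fixed by "setting the probability of α error at 0.05, 1-β = 0.80, and 5 groups", so 0.05 is not divided among outcomes.

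**The concern.** The sample-size section treats muscle power as the variable that decides efficacy. The outcome section does not. As written, a significant result on any member of the leg-press family could be reported as a result on a primary outcome, and the nominal 5% does not describe how often that happens by chance.

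The five-group test also gives weak protection to the question the trial was set up to answer. The stated aim is the role of supervision and motivation, which concerns differences among the four exercise arms. If exercise simply beats control, the overall test is significant for that reason and no longer guards the comparisons between exercise arms.

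**Working it through.** **1. The plan's own figure.** For a group-by-time interaction with k = 5 groups, m = 4 assessments and f = 0.43/2 = 0.215, take λ = N·f²·m/(1 − ρ), df1 = (k − 1)(m − 1) and df2 = (N − k)(m − 1). With ρ = 0 and N = 100:

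- λ = 100 × 0.046225 × 4 = 18.49
- df1 = 12 and df2 = 285
- power = 0.814 (N = 95 gives 0.787)

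So 100 is reproduced with one test at the full 0.05. The values ρ = 0 and m = 4 are assumptions, since the article states neither.

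**2. Counting the family.**

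- Isometric test: 2 angles × (maximal force, one RFD interval, RFDmax) = 6.
- Force–velocity test: 2 intercepts, maximum power, force at maximum power and velocity at maximum power = 5.
- Listed total: 6 + 5 = 11.

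Two of the 11 are not separate tests. On a straight line F = F0(1 − v/V0), power is F0·v(1 − v/V0). It peaks at v = V0/2, where F = F0/2 and power = F0·V0/4. Force and velocity at maximum power are therefore half the intercepts and give identical F tests. That leaves 11 − 2 = 9. More RFD intervals raise the count. Pooling the two angles lowers it to 3 + 3 = 6.

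**3. Chance of at least one false positive in the family**, one five-group test per variable at 0.05, no true differences:

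| Case | Chance |
|---|---|
| 9 variables, correlation 0.8 (simulated) | about 17% |
| 9 variables, correlation 0.3 (simulated) | about 33% |
| 9 independent variables, 1 − 0.95⁹ | 37% |
| 6 independent variables, 1 − 0.95⁶ | 26% |

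The independent rows are upper references only, because these variables are correlated and power is itself a function of the intercepts. The correlation range is an assumption; the article gives none.

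**4. Adding the two other primary outcomes with a named test**, adverse events (Chi-squared) and adherence (ANOVA), taken as independent:

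- 1 − (1 − 0.17) × 0.95² = 25%
- 1 − (1 − 0.33) × 0.95² = 40%

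**5. Comparisons among exercise arms.** Suppose the four exercise arms are truly equal, control differs, and the six pairs are tested without adjustment. With 96 evaluable participants (120 × 0.80) the error degrees of freedom are 96 − 5 = 91 and the two-sided critical t is 1.986. The chance of at least one false pair is P(q(4, 91) > 1.986 × √2) = 0.20, for each variable at one time point.

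**The case against.** A reader might infer something stronger: that four primary domains are all tested at 0.05 at three follow-up visits, so that a false primary finding is more likely than not. The article does not support this, for four reasons.

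- **Not all domains are tested.** Costs, QALY differences and the cost-effectiveness ratio are to be calculated with no significance test named, and falls are presented as rates and numbers.
- **Visits do not each add a test.** Visit is a factor in one model. Week 13 is a single session, and whether it includes the leg press cannot be confirmed from the text, because the figures are not shown.
- **The listed count of 11 overstates the distinct tests**, as step 2 shows. Unilateral testing does not double it either, since nothing says that both legs are analysed.
- **The resulting risk is below one half** on the omnibus tests.

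The post-hoc method may also be set in an analysis plan that is not shown, and a 0.05 threshold is compatible with adjusted p-values. The 20% in step 5 is therefore conditional. Further, safety, adherence, efficacy and cost-effectiveness are posed as separate questions, and nothing says that the trial succeeds if any one of them is significant.

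All of this stands, but it does not remove the point. The article itself lists an unranked primary efficacy family and itself fixes 0.05 for every test. Choosing the decisive variable and visit belongs in the protocol and is not a detail to be filled in later.

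**Conclusion.** The point holds for the leg-press family. Followed as written, the plan gives a false-positive chance on its primary efficacy outcome of about 17% to 33%, against a nominal 5%. This assumes nine distinct variables, one overall test for each, and correlations from 0.8 to 0.3. Counting adverse events and adherence takes it to about 25% to 40%. A separate 20% per variable applies to the exercise-arm pairs, but only if the post-hoc tests are unadjusted and exercise differs from control. The documents do not show that a false positive is likely in the sense of exceeding one half, nor that every primary domain is tested at every visit.

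**What to change.** Before unblinding:

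- Name maximum muscle power from the force–velocity test at week 25, the end of the intervention, as the single confirmatory efficacy variable. It is the listed variable closest to the quantity used for the sample size.
- Test the supervision and the motivation contrast on it, with Holm control at 0.05.
- Relabel the other leg-press variables and visits as secondary, reported with confidence intervals and no confirmatory claim.
- Keep safety, adherence and costs as separate objectives that are estimated.

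**Cost.** Only one efficacy variable remains confirmatory. The 0.43 is an effect of home-based exercise, so the sample-size section does not establish power for contrasts between exercise arms, and the protocol should say so. As an illustration, assume 96 evaluable participants, about 38 on each side of a contrast (2 × 96/5), and a difference as large as 0.43. Power at Holm's first step (0.025) is then about 35%, or about 46% with a baseline correlation of 0.5, and true differences between exercising arms may be smaller. The trial is registered and recruiting, so the change must be recorded as a dated amendment, with the registry entry checked against it.

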**Discussion:**

The findings of this trial might provide valuable insights into the role of supervision and motivational strategies on the effectiveness of exercise programs for older adults. Additionally, the study could contribute to developing cost-effective interventions, supporting the design of future public policies for healthy aging.

**Trial registration:**

NCT05619250. Registered 16 November 2022.

**Supplementary Information:**

The online version contains supplementary material available at 10.1186/s12877-024-04868-8.

## Background

Population aging is a highly prevalent phenomenon worldwide. Projections indicate that the global population aged 60 and above is expected to increase by more than 3 times, reaching nearly 2 billion by 2050 [1]. Aging is linked to physiological and functional impairments that can contribute to an increased risk of frailty, disability, and falls, increasing the susceptibility to chronic diseases [2–5]. It is well known that physical activity is an effective factor in reducing the risk of all-cause mortality and preventing the loss of intrinsic capacity (*i.e.,* the combination of all physical and mental capacities of a person) during aging [6–9]. There is strong evidence showing that regular exercise reduces age-related physical and mental decline [10, 11]. Specifically, multicomponent exercise interventions appear as an effective strategy for improving major outcomes such as muscle strength and mass or gait ability, as well as for reducing the incidence of falls and attenuating functional impairments [12–15]. Nevertheless, a large proportion of the population remains physically inactive. Particularly, a population-based study showed that only 15% of men and 10% of women aged ≥ 70 years achieved physical activity guidelines [16].

Although supervised center-based exercise interventions (herein referred to as supervised exercise for simplicity) are commonly prescribed to older adults, on some occasions feasibility can be limited by economic constraints, convenience, and access or time commitments [17, 18]. Under this context, unsupervised home-based exercise programs (herein referred to as unsupervised exercise) emerge as a potential alternative, and indeed different meta-analyses have shown that, compared with no exercise, unsupervised exercise can be effective for improving components of health and fitness in older adults [19, 20]. However, to date, there is no consensus on whether unsupervised exercise programs can be as effective –or even more cost-effective– than supervised ones. Some studies have shown greater benefits on different health variables with professionally supervised exercise programs compared to those performed autonomously at home [21–23]. On the other hand, other studies indicate that unsupervised exercise programs can be as effective as supervised ones [24–26]. For instance, Fisher et al. [27] found that supervised resistance exercise induces slightly greater muscle strength gains compared to unsupervised exercise in teenagers and adults, with minimal to no extra benefits on body composition. If their safety and cost-effectiveness are confirmed, unsupervised exercise programs would represent an alternative for increasing the accessibility of exercise for older adults, which would be of relevance for future public health policies. Nonetheless, most studies comparing supervised and unsupervised exercise have applied different interventions in each group (*e.g.,* different training types, duration, intensity, and exercise selection) [21]. Additionally, groups are often labeled as ‘supervised’ despite including some unsupervised sessions, and vice versa [28]. Therefore, well-designed randomized controlled trials (RCTs) that equalize exercise dose (*i.e.,* type, frequency, intensity, and volume) between both groups are warranted to draw definite conclusions on the role of supervision on the effectiveness of exercise programs.

One of the factors that could moderate the effectiveness of exercise programs is adherence. In this regard, a recent meta-analysis by our research group showed that adherence to unsupervised exercise programs is usually low [29], probably due to a lack of motivation. Applying motivational strategies might help increase adherence to exercise programs, which could eventually result in greater training-induced adaptations [30–32]. Some studies have analyzed the impact of motivational strategies during exercise programs in older adults [33, 34]. However, these studies analyzed the influence of motivational strategies in supervised or unsupervised exercise interventions separately, but never before have they been examined in a single study.

The Promoting Training Programs for Health (PRO-Training) trial aims to cover all the abovementioned research gaps. The main goal of this RCT will be to determine the impact of supervision and motivational strategies on the safety, adherence, efficacy, and cost-effectiveness of different exercise programs for improving physical and mental health in older people.

## Methods

This protocol is reported according to the Standard Protocol Items: Recommendations for Interventional Trials (SPIRIT statement) [35] to ensure that all relevant information is included. A checklist is provided including this information (see Supplementary Table 1). The participant timeline recommended by SPIRIT includes the schedule of enrolment, interventions, and assessments (Fig. 1).

**Fig. 1 Fig1:**
[figure not shown]
SPIRIT flow chart of study procedures. SDT: Self-Determination Theory; SUP: Supervised exercise without motivational intervention; SUP + : Supervised exercise with motivational intervention; -T1: enrolment of participants before assessments; T1: baseline assessment at 0-week; T2: mid-intervention assessment at 13-week; T3: post-intervention assessment at 25-week; T4: follow-up assessment at 49-week; UNSUP: Unsupervised exercise without motivational intervention; UNSUP + : Unsupervised exercise with motivational intervention

### Study design

The study will follow a single-blind randomized, parallel design. Participants will be randomized into 5 groups (Fig. 2): 1- Control group (CON), 2- Supervised exercise without motivational intervention (SUP), 3- Supervised exercise with motivational intervention (SUP +), 4- Unsupervised exercise without motivational intervention (UNSUP) and 5- Unsupervised exercise with motivational intervention (UNSUP +). Assessments will be conducted at baseline (week 0), mid-intervention (week 13), at the end of the intervention period (week 25), and 24 weeks later (week 49).

**Fig. 2 Fig2:**
[figure not shown]
Flowchart of the study protocol. CON: Control group, SUP: Supervised exercise without motivational intervention, SUP + : Supervised exercise with motivational intervention, UNSUP: Unsupervised exercise without motivational intervention, UNSUP + : Unsupervised exercise with motivational intervention

The study will be conducted at the University of Castilla-La Mancha (Spain). It will be reported in accordance with the Consolidation Standards of Reporting Trials (CONSORT) statements for cluster RCTs and Standard Protocol Items: Recommendations for Interventional Trials [36].

### Sample size

The sample size was determined by a priori power analysis using G ∗ Power 3.1.9.4 software. Input parameters were entered considering repeated measures ANOVA (group by time interaction), setting the probability of α error at 0.05, 1-β = 0.80, and 5 groups. The standardized mean difference used for calculations was 0.43, based on the effect of home-based exercise on lower-body muscle power in older adults reported in a previous meta-analysis [19]. The model indicated a total sample size of 100 individuals, and considering a dropout rate of 20%, we finally decided to enroll 120 participants.

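### Enrolling 120 does not cover 20% dropout from a requirement of 100: it leaves 96, and covers 16.7% dropout at most

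*Protocol article*

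**What the plan says.** The calculation is in the protocol article under Methods, Sample size. It was done in G*Power for a repeated-measures model: "Input parameters were entered considering repeated measures ANOVA (group by time interaction". The error rates and number of arms follow: "setting the probability of α error at 0.05, 1-β = 0.80, and 5 groups". The effect size is given as a standardized mean difference: "The standardized mean difference used for calculations was 0.43, based on the effect of home-based exercise on lower-body muscle power in older adults". The result and the dropout allowance stand in one sentence: "The model indicated a total sample size of 100 individuals, and considering a dropout rate of 20%, we finally decided to enroll 120 participants".

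The Recruitment section and the abstract repeat 120 as the target. No other section gives a different dropout rate, a different required number or a different inflation. The Study design section confirms five arms and four assessments, at weeks 0, 13, 25 and 49.

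**The concern.** The sentence gives a required number, a loss rate and an enrolment target, and one of the three must be wrong given the other two. The natural reading is that 100 participants will remain once 20% have left. They will not: 96 will, fewer than the plan itself says are needed for 80% power.

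What is at stake is a headline design figure. The enrolment target and the stated power will be carried into the results paper. If dropout turns out as planned, the trial will finish below its own requirement while reporting that dropout was allowed for. All three figures are printed in the article, so its condensed form does not explain the mismatch.

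**Working it through.** **Inputs.** From the Sample size section: required total N = 100, dropout d = 0.20, enrolment 120, α = 0.05, power 0.80, five groups (k = 5), test of the group-by-time interaction, standardized mean difference 0.43. From the Study design section: four assessments. Not stated, and so assumed where needed: equal group sizes, the number of measurements entered (m), the correlation between measurements (ρ), sphericity, and the conversion of 0.43 to Cohen's f.

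**Step 1: reproduce the plan's 120.**
- N × (1 + d) = 100 × 1.20 = 120.

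This is the plan's figure. It takes 20% of the number required and adds it on, instead of allowing for 20% of the number enrolled.

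**Step 2: apply the stated dropout to the stated enrolment.**
- 120 × (1 − 0.20) = 96 remaining, or 96/5 = 19.2 per arm, against 100/5 = 20 required.
- Enrolment that leaves 100: 100/(1 − 0.20) = 125, or 25 per arm. The gap is 125 − 120 = 5.
- Dropout that 120 does cover: 1 − 100/120 = 16.7%.

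This step needs no assumption beyond the plan's own figures.

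**Step 3: power at 96.** For the interaction, power is the upper tail of a noncentral F with
- df1 = (k − 1)(m − 1)
- df2 = (N − k)(m − 1)
- λ = f² N m/(1 − ρ)

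Two routes give the size of the loss.

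*(a) Take 100 as giving exactly 80%.* Solve for the λ that gives 0.80 at N = 100, then multiply it by 96/100, because λ is proportional to N.

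| Measurements m | λ at N = 100 | λ at N = 96 | Power at N = 96 |
|---|---|---|---|
| 2 | 12.54 | 12.04 | 78.0% |
| 3 | 15.64 | 15.02 | 77.9% |
| 4 | 17.98 | 17.26 | 77.9% |

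This route needs neither f nor ρ, because both are absorbed into λ.

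*(b) Use one explicit setting that yields 100.* Take f = 0.43/2 = 0.215, m = 4, ρ = 0.
- N = 98: λ = 0.215² × 98 × 4 = 18.12, power 80.3%. This is the smallest N that reaches 80%, and equal groups of 20 bring it to 100.
- N = 100: λ = 18.49, power 81.4%.
- N = 96: λ = 17.75, power 79.3%.

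The two routes put the power at 96 at about 78–79%, which is 1 to 2 points below 80%.

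**Step 4: can the 100 itself be faulted?** Other admissible values also give 100 in equal groups: f = 0.215 with m = 2 and ρ of 0.27 to 0.29, or with m = 3 and ρ of 0.12 to 0.15. With ρ = 0.5 and f = 0.215 the minimum would instead be 70, 59 or 51 for m = 2, 3 or 4. The article names no correlation, so nothing in it selects 0.5 over the values that give 100.

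**The case against.** **The effect is trivial.** The loss is 1 to 2 points of omnibus power, and the shortfall is five people enrolled or four completing. This stands, and it limits the weight of the point. It does not make the sentence correct.

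**Analysis by intention to treat softens it.** The Statistical analysis section plans to include all randomized participants where possible and to explore multiple imputation, so the number analysed need not be 96. That is true, but it does not repair the arithmetic. The plan itself chose to allow for dropout, and the allowance does not do what is said of it.

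Three stronger readings are tempting, and the documents do not support them.

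- *The 100 is wrong.* A reader may try the calculation at a correlation of 0.5, get 51 to 70, and conclude that 100 does not follow from 0.43. That correlation is not in the article, and Step 4 shows unstated but admissible inputs that do give 100. The missing inputs are detail that an article may leave to the full protocol. The two complaints also cannot be made from the same premise: at ρ = 0.5 with f = 0.215, 96 participants would have 92.7%, 97.2% or 99.0% power for two, three or four measurements.
- *Power falls well below 78% because more people are lost by week 49.* The article gives no loss rate other than 20%, so a larger loss would be invented.
- *The plan claims 80% power for 0.43 between two arms.* The Sample size section names the group-by-time interaction as the test, so the article makes no such claim.

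**Conclusion.** The concern holds for the dropout allowance and no further. With 20% dropout, 120 enrolled leaves 96, below the 100 required. The matching enrolment is 125, and 120 matches a dropout of 16.7%. These results rest only on figures printed in the Sample size section and are certain.

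The cost in power is small: about 78–79% instead of 80% for the omnibus interaction. That figure assumes equal groups, sphericity, an analysis of the 96 remaining participants, and that the plan's 100 does correspond to about 80% power. It is a wrong statement about a figure the trial relies on, worth correcting because the correction is easy. It is not evidence that the design is inadequate.

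**What to change.** Keep 120 and change the one sentence, in either of two ways:

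- state that enrolling 120 allows for up to 16.7% dropout while keeping 100; or
- keep the 20% rate and state that 96 evaluable participants are expected, with about 78–79% power for the omnibus group-by-time interaction.

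The second form should name the settings behind the quoted power, since it depends slightly on them. The cost is one sentence and, in the second form, a stated power 1 to 2 points lower. Recruitment, design and analysis are unchanged. Raising enrolment to 125 would also reconcile the figures, but a shortfall of this size does not call for it.
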